### Procedure

Smokers residing in Germany will be recruited by a market research company using the PAYBACK panel, which exists since 2007. PAYBACK panelists are recruited through PAYBACK, which is the largest customer loyalty program, covering half of the German households. The panel is composed of more than 130.000 adults and is one of the largest online access panels in Germany. Panel members will be screened for eligibility by email (that contains a link to the digital questionnaire). Eligible participants will be required [1] to be at least 18 years old, [2] to have smoked cigarettes on a daily basis in the past 30 days, [3] to intend to quit smoking in the following month and [4] to provide informed consent prior to participation. Contact details of participants will be transferred to the study site twice a week. To improve adherence to the intervention protocols, referred smokers will be contacted by telephone prior to baseline assessment. During this call, they will again be informed about the procedure of the study and possible questions will be answered. Consented participants will complete the digital baseline questionnaire which will validate eligibility criteria before randomization. At least two weeks after completing the screening questionnaire, participants will either receive the self-help brochure or a call from a quitline counsellor. Three and 12 months after baseline assessment, participants will obtain another email with links to the respective questionnaires.

Participants are obliged to give study consent prior to accessing the online questionnaires. For convenience, all participants will be offered the option to complete the questionnaires via telephone interviews. Participants will receive a €25 voucher for the baseline assessment and a €15 voucher for the post and follow-up assessment respectively. For taking part in the biochemical verification, an additional remuneration of €30 will be offered. Moreover, several shopping vouchers will be raffled among participants who complete the entire study.

### Randomization

Randomization will be conducted by a research staff member. To ensure equal distribution of participants concerning selected key characteristics, randomization will be stratified based on four strata: number of cigarettes smoked per day (1–10/11–20/21–30/> 30 cigs per day), sex (female/male/diverse), age (18–30/ 31–64/> 64 years old) and level of education (low/middle/high) as reported by participants at baseline. The numbers of participants receiving each intervention are closely balanced within each stratum by performing a separate randomization procedure using permuted blocks (with each recruitment session as a block) of varying length. The first study participant per block (ordered randomly using the RAND function, Microsoft Excel) is randomized into the intervention group, the second one into the control group and so on. The randomization procedure is documented and maintained using a list which contains all possible combinations of strata and their levels as well as the number of participants in each group per strata combination. If the groups differ due to an imbalance in a certain strata combination (difference > 5 participants), the next participant with the respective strata combination will be allocated to the underrepresented group until an equal distribution is achieved.

Allocation concealment will be ensured, as participants will not be assigned to one of the study conditions until baseline measurements have been completed. Due to the nature of the intervention, neither participants nor staff can be blinded to allocation. In the study material, participants will be informed about the two study conditions. However, participants will be blinded to the study hypothesis in terms of which intervention is considered active.

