## Methods

### Study design

The present evaluation is designed as a parallel-group, superiority, two-arm randomized controlled trial with 1:1 allocation ratio. The evaluation comprises three assessments within a period of approximately one year. Data collection will take place at baseline, three months (post assessment) and twelve months (follow-up assessment) after baseline assessment. The study design and participant flow are outlined in the Consolidated Standards for Reporting Trials (CONSORT) diagram (Fig. 1). After giving informed consent and completion of the baseline survey, participants will be randomly assigned to the intervention or control group. In the intervention group, participants will receive telephone counselling from counsellors of the national German Smokers Quitline, while in the control group they will be provided with a self-help brochure to support smoking cessation. Self-help materials were chosen as treatment in the control condition, as participants may have a benefit compared to receiving no intervention [20]. Moreover, it is considered unethical to recruit participants for a smoking cessation treatment when subsequently not offering an intervention. Providing an alternative intervention for the control group may also help achieve comparable response rates. To allow correction for any overreporting of abstinence, abstinence will be biochemically verified for a random sample of study participants who report abstinence at 12-month follow-up.

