### Sample size calculation

To calculate the required sample size, a power analysis was carried out using the software G*Power [21]. Based on previous studies examining the effects of telephone smoking counselling and the use of self-help materials on seven-day-point-prevalence abstinence rates [15], a small effect size was expected. Assuming a significance level of 5% and statistical power of 0.8, the estimated required sample is *N* = 700 participants (350 participants per study condition). The calculated sample size was corrected by a 30% dropout rate [7], resulting in a total sample size of *N* = 910 enrolled participants.

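### Every block starts with the intervention arm and catch-up allocations are forced, so some assignments are foreseeable and, depending on what a block is, the arms may end well away from 1:1

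*Protocol article*

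**What the plan says.** All of this is in the protocol article, under Methods.

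- **Study design** describes a "two-arm randomized controlled trial with 1:1 allocation ratio".
- **Sample size calculation** ends with 30% added for dropout, "resulting in a total sample size of *N* = 910 enrolled participants".
- **Randomization** stratifies on cigarettes per day (4 levels), sex (3), age (3) and education (3). It says the arms are kept close within every stratum by running a separate procedure with permuted blocks, and that each recruitment session forms a block. Within a block the participants are sorted by Excel's RAND function. The first in that order "is randomized into the intervention group, the second one into the control group and so on".
- A list holds the running count of each arm in each strata combination. When a combination differs by more than 5, "the next participant with the respective strata combination will be allocated to the underrepresented group until an equal distribution is achieved".
- The same section states: "Allocation concealment will be ensured, as participants will not be assigned to one of the study conditions until baseline measurements have been completed". It adds that neither participants nor staff can be blinded.

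**The concern.** A permuted block normally randomises which arm comes first, so odd or unfinished blocks lean either way and the leanings cancel. Here the first position always belongs to intervention, so the leanings add up. A block of one is not randomised at all. With many strata and small sessions, single-person blocks could be common.

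Two things are at stake. One is balance: sparse factor levels, such as smokers of more than 30 a day or people over 64, could collect in the intervention arm, which is what stratification is meant to prevent. The other is foreseeability: in single-person blocks and during forced catch-up, the next arm can be read from the rule and the tally. Staff are unblinded and abstinence is mainly self-reported, with CO checks planned in 20% of 12-month abstainers, so unpredictable allocation is the main protection of the primary comparison.

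**Working it through.** **Inputs from the article.** N = 910, reproduced as 700 × 1.30. At 1:1 this is 455 per arm. Strata: 4 × 3 × 3 × 3 = 108, so 910/108 = 8.4 people per stratum. Contact details reach the site twice a week (Procedure) and recruitment runs from October 2021 to June 2022 (Data collection and management). That is about 39 weeks, or at most about 2 × 39 = 78 sessions of 910/78 ≈ 12 people, if each transfer counts as a session.

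**Assumptions (not in the article).** 20, 39 or 78 sessions. Shares: cigarettes per day 30/50/15/5%; sex 50/49.5/0.5%; age 15/75/10%; education 20/40/40%. Under these shares only about 70 strata are occupied, so 910/70 = 13 people per occupied stratum.

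**Step 1: what one block does.** A block of m people in random order sends ⌈m/2⌉ to intervention and ⌊m/2⌋ to control.

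- m even: excess 0, and each person has probability 1/2.
- m odd: excess +1, always to intervention.
- m = 1: intervention with certainty, unless a catch-up is running.

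**Step 2: a stratum filled only by single-person blocks.** The first six people go to intervention. The difference is then 6, which exceeds 5, so the next six are forced to control. The difference runs 0, 1, …, 6, 5, …, 1 and then repeats, with mean (0+1+2+3+4+5+6+5+4+3+2+1)/12 = 36/12 = 3. A stratum of six or fewer filled this way has no controls. As a rough check, 70 occupied strata × 3 = 210 excess intervention participants.

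**Step 3: simulation of the whole rule**, including catch-up:

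| Reading of block | Intervention vs control (mean) | Predetermined assignments | >30/day in intervention | Aged >64 in intervention |
|---|---|---|---|---|
| Stratum within session | about 553–558 vs 352–357 | 42–78% | over 80% | over 80% |
| Whole session | about 458–463 vs 447–452 (SD about 6) | about 8% (forced) | 51–52% | 51–52% |

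The first row's excess is 553 − 357 = 196 to 558 − 352 = 206, in line with the rough 210. For the second row, about half of all sessions have odd size, so the excess before catch-up is about 20/2 = 10 to 78/2 = 39. Catch-up reduces it to 458 − 452 = 6 to 463 − 447 = 16.

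**Step 4: other shares.** With blocks within stratum and session, two other skewed sets of shares give a mean excess of 168–213 and 36–81% predetermined. Equal shares over all 108 strata, an extreme case, give 386–428 and 71–93%. With whole-session blocks, all three sets give a mean excess of 4–35 and 2–9% forced.

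**Step 5: cost in precision.** Relative efficiency is 4·n_I·n_C/N². At an excess of 220 (565 vs 345) it is 4 × 565 × 345/910² = 0.94.

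**Step 6: who could foresee.** Table 1 shows cigarettes per day and socio-demographic data collected already at screening. Procedure has participants telephoned before baseline. Anyone who holds those data and the tally can identify a forced allocation, or a person alone in a block, before the baseline questionnaire is complete.

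**The case against.** A reader might infer that allocation is deterministic alternation throughout. It is not. Alternating down a randomly sorted list is a random split, so only single-person blocks and forced catch-up are predetermined.

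A reader might also infer that the trial cannot be near 1:1. That depends on the reading of block. The wording about a separate procedure in each stratum points to blocks within strata. But the text calls each session a block, and a per-stratum tally with a catch-up rule makes good sense if the whole session is the block. On that reading the lean exists only on average, control can end as the larger arm, and sparse factor levels stay near half and half. Under either reading the catch-up rule holds the difference in a stratum to about 6.

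Finally, a reader might infer that concealment is absent, or that staff could re-sort the list until they liked it. Nothing in the article shows this. Consent and a self-completed baseline that validates eligibility precede assignment, and the procedure is documented. A condensed article may also leave the separation of enrolling and allocating staff to the full protocol.

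These points stand, as does the modest loss of precision. The planned inclusion of confounders in the analysis would deal with part of any measured imbalance, although it depends on baseline differences and does not commit to the four stratification factors. None of this removes the fixed first arm, the foreseeable forced allocations, or the reliance on timing alone as the basis for concealment.

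**Conclusion.** The point holds, with a size that depends on the meaning of block. With blocks within stratum and session, the reading the wording favours, the rule as written contradicts both the 1:1 ratio and the claim of close balance within strata: about 550–560 against 350–360, with 42–78% of assignments predetermined and over 80% of the heaviest smokers and of the over-64s in intervention. With whole-session blocks the tilt is a few participants on average and about 8% of assignments are forced. These figures rest on assumed factor shares and 20 to 78 sessions. The direction of the tilt does not: it follows from the fixed first arm. Concealment is unsupported by the reason given, rather than shown to have failed. The main problems are foreseeability and possible imbalance in sparse levels; lost power is minor.

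**What to change.** Define the block, and replace both the fixed-first-arm rule and the catch-up rule with a scripted procedure (stored seed) that randomises arm order. Two forms would serve:

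- randomly permuted blocks of random size, carried across sessions, within a few strata; or
- minimisation on the four factors with a random element.

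Release each arm only after that participant's baseline record is locked, and base the concealment statement on this.

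Before enrolment the cost is a short script and an amendment of one paragraph, with no extra participants. The price is slightly less exact balance in very small strata.

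If enrolment has already run under the published rule, the sequence cannot be repaired. Then report allocation by stratum and session, state which definition of block was used, adjust the primary model for the four stratification factors regardless of baseline tests, and restate the concealment claim to say what staff could and could not foresee.

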### Data collection and management

Participants will be recruited consecutively between October 2021 and June 2022. Therefore, data collection will take place at different time points (at baseline, three months and twelve months after baseline assessment) over a period of approximately two years. Data will be collected via online questionnaires using the software SoSci Survey [46]. It is expected that the majority of questionnaires will be administered digitally (compared to phone interviews). In order to biochemically verify abstinence, 20% of study participants who will report abstinence at 12-month follow-up and who consented to participate will be randomly selected. Research staff will meet participants at their preferred location and will collect breath carbon monoxide (CO) using a portable CO monitor.

Once a participant is enrolled, the study site will make every reasonable effort to follow the participant for the entire study period. Various procedures will be used to reduce attrition, including reminder emails and calls, flexible scheduling of the counselling sessions, and incentives for completing the questionnaires. It is expected that the rate of loss-to-follow-up will not exceed the calculated 30%. To enhance validity of data, multiple methods will be used to assess intervention adherence including the phone call prior to enrolment in order to answer possible questions and questionnaire items on the use and acceptability of the received intervention at 3-month post assessment.

All participant data is handled in accordance with the General Data Protection Regulation (GDPR). All data will be maintained confidentially before, during, and after the trial and is stored securely at the study site with access only by dedicated study team members. All substantial procedures are described in the application for the Ethics Committee and can be provided on request. The final data set will be stored for 10 years after completion of the study. A data monitoring committee is not considered necessary as participants are not blinded to the study conditions and as this is a short-term, non-invasive intervention with the opportunity to quit at any time without any negative consequences or side-effects.

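### The reason given for leaving all staff unblinded covers participants, counsellors and allocation staff, but not those who make reminder calls or conduct telephone outcome interviews

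*Protocol article*

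**What the plan says.** The Randomization section makes one general statement on masking, with the nature of the intervention as its reason: "neither participants nor staff can be blinded to allocation". It makes no exception for outcome assessment. The same section says of allocation: "Randomization will be conducted by a research staff member".

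The treatment comes from a different body. Under Study design, "participants will receive telephone counselling from counsellors of the national German Smokers Quitline".

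Follow-up involves contact with staff in at least two ways that bear on the primary outcomes:
- Procedure: "all participants will be offered the option to complete the questionnaires via telephone interviews".
- Data collection and management: measures against attrition, "including reminder emails and calls".

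Statistical analyses states that participants whose smoking status cannot be determined at follow-up are counted as smokers in the intention-to-treat analysis. It adds a complete-case analysis. Loss to follow-up is expected to be no more than 30%.

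**The concern.** The statement is broader than its reason. A participant knows whether counselling calls or a brochure arrived, a counsellor knows who is being counselled, and whoever allocates or passes on the allocation knows the arm. For these people the nature of the intervention settles the matter. It does not settle it for someone who phones a non-responder or reads out a questionnaire.

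Two outcome routes are exposed. The more important is reminder effort. When non-response is scored as smoking, each abstainer brought back by an extra call moves from smoker to abstinent in the primary analysis. If one arm were chased harder, even without intent, its abstinence rate would rise with no treatment effect. Online completion does not close this route, because reminders influence who completes the questionnaire at all. The second route is the telephone interview, where self-reported abstinence is given to a person who may know the arm.

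**Working it through.** **Does the stated reason reach follow-up staff?** No figure in the plan is at stake here, so the check is a reading of the sections side by side.

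| Role | Must know the arm? | Basis |
|---|---|---|
| Participant | Yes | Receives calls or a brochure |
| Quitline counsellor | Yes | Delivers the calls (Study design; Interventions) |
| Person allocating, or arranging counselling | Yes | Randomization; Data collection and management |
| Reminder caller | No reason given | Data collection and management |
| Telephone outcome interviewer | No reason given | Procedure |

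At 3 months the questionnaire includes items on use and acceptability of the received intervention, which would reveal the arm to an interviewer. Table 1 lists these items at the post assessment only, not at 12 months. Asking smoking status first would protect the outcome answer at 3 months.

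**What would a response gap do?** Illustration only.

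Inputs from the article: 910 randomised 1:1, so 910 / 2 = 455 per arm; planned loss 30%, so 70% response; missing = smoker; 7% and 10% long-term abstinence cited in the Background.

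Assumptions of mine: no true effect; one arm responds at 70% and the other at 75% or 80%; extra responders are abstinent as often as other responders; two-sided 5% pooled two-proportion z-test.

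Formula: observed abstinence = abstinence among responders × response rate.

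At 70% response, an observed 7% implies 0.07 / 0.70 = 10.0% among responders, and an observed 10% implies 0.10 / 0.70 = 14.3%.

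| Abstinent among responders | Response | Observed abstinence | Spurious difference | Type I error |
|---|---|---|---|---|
| 10.0% | 75% v 70% | 7.5% v 7.0% | 0.5 points | 6.0% |
| 14.3% | 75% v 70% | 10.7% v 10.0% | 0.7 points | 6.4% |
| 10.0% | 80% v 70% | 8.0% v 7.0% | 1.0 point | 8.8% |
| 14.3% | 80% v 70% | 11.4% v 10.0% | 1.4 points | 10.7% |

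Worked row (80% v 70%, 10.0% among responders):
- Difference d = 0.080 − 0.070 = 0.010; pooled p = 0.075.
- SE under the null = √(2 × 0.075 × 0.925 / 455) = 0.01746; the unpooled SE is also 0.01746.
- Upper-tail rejection: 1 − Φ((1.96 × 0.01746 − 0.010) / 0.01746) = 0.0826.
- Lower-tail rejection: 0.0057.
- Sum: 0.0883.

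A gap of 5 points is 0.05 × 455 ≈ 23 participants, and one of 10 points is about 46. If none of the extra responders were abstinent, the spurious difference would be zero.

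**Would the plan's own analyses show it?** Under this model abstinence among responders is equal in both arms (for example 10.0% v 10.0%), so an analysis of responders shows no difference. A gap between the primary and complete-case results would be a warning sign.

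**The case against.** The strongest reply is that little harm has been shown. Much of it stands.

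- **The article does not say who makes the calls or interviews, or that these people know the arm.** Correct. A reader might infer from the general sentence that follow-up is in fact done by staff who know the arm. The text supports only that nothing keeps the arm from them.
- **Allocation could easily be locked away with one person.** A reader might infer this from the list described under Randomization. That list is a tally of numbers per combination of strata; the article does not say who holds individual allocations.
- **Some study-site work is arm-specific.** Flexible arrangement of counselling appointments stands beside reminders among the measures against attrition. Full separation of tasks may not be possible, so masking is proposed only where feasible.
- **A response gap may have nothing to do with staff.** Participants are unblinded and receive very different contact. Masking staff would not remove that part.
- **There are safeguards.** Most questionnaires are expected to be completed online, both arms get the same emailed links and vouchers, controls get an alternative intervention partly to keep response comparable, and a complete-case analysis is planned.
- **CO verification.** A reader might extend the point to the CO visits. The documents do not support that: CO is an instrument reading with an 8 ppm cut-off, in a random 20% of consenting self-reported abstainers. At 7% and 10% abstinence this is (0.07 + 0.10) × 455 ≈ 77 abstainers and about 15 tests, taken after the self-report.
- **Reminder schedules and item order are operational detail.** An article may leave these to the full protocol, so their absence is no fault. They appear below only as part of the remedy.

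What remains is a positive statement, with a reason attached, that goes further than the reason allows.

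**Conclusion.** The concern holds in a limited form. The claim that staff cannot be blinded is justified for counsellors and for those handling allocation or counselling appointments. It is not justified for reminder calls and telephone outcome interviews. Scoring missing status as smoking gives unequal follow-up effort a direct route to the primary abstinence rates.

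Under the assumptions listed, the type I error would be about 6.0–6.4% at a 5-point response gap and 8.8–10.7% at 10 points. The gaps are assumed, and nothing in the article predicts them. The figures measure the effect of differential response under missing = smoker. To read them as the bias caused by unblinded staff would go beyond the documents. Because the safeguards are real and masking would be incomplete, this is a low-cost improvement and does not threaten the trial's validity by itself.

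**What to change.** - Limit the sentence under Randomization to participants, counsellors, and staff who handle allocation or counselling appointments.
- State that existing staff make reminder calls and conduct telephone outcome interviews from contact lists without the arm, where feasible.
- Apply the same reminder sequence and the same maximum number of contacts in both arms.
- In telephone interviews, record smoking status before the items on the received intervention.

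Cost: restricted access to allocations and some division of tasks among existing staff. No larger sample or additional assessment is needed. Masking will be partial, because some participants will disclose their arm.
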